### **Safety**

AZD4017 has been studied in healthy human volunteers and is tolerated when given in single doses up to 1500mg and in multiple doses up to 900mg for periods of up to 9 days. A Phase IIa study of 28 days duration has been conducted in patients with raised intraocular pressure; 7 subjects received 200 mg once daily AZD4017 for up to 28 days and 19 subjects received 400 mg twice daily AZD4017 for up to 28 days. The most commonly reported AE in the studies with AZD4017 were gastrointestinal disorders and headache and were of mild to moderate intensity. Previous safety studies in healthy volunteers also reported an increase in ACTH and dehydroepiandrosterone sulfate levels. However, cortisol and testosterone levels were not changed. As the proposed pilot trial is relatively short, we will measure dehydroepiandrosterone sulfate and testosterone. However, blood samples will be stored allowing ACTH and cortisol to be measured in any patient showing evidence of hypothalamic-pituitary-adrenal (HPA) axis activation.

Other safety laboratory analyses showed no clinically relevant changes. No clinically relevant changes or trends were seen in vital signs or in ECG results in previous safety studies.

Although other 11 $\beta$ -HSD1 inhibitors have been trialled in patients with T2DM and were safe and well-tolerated [32, 33], AZD4017 has not been tested in this patient cohort. This preliminary pilot trial will therefore evaluate safety by monitoring validated safety variables of T2DM (e.g. BMI, waist-hip ratio, BP, HbA1c and lipids) and AZD4017 (e.g. FBC, LFT, eGFR, U+E, adrenal and thyroid function). Further information regarding non-clinical data and previous clinical studies can be found in the AZD4017 IB.

Data collected will be used to inform powering and feasibility of a future confirmatory trial.

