#### **6.4.3. Randomization process**

Treatment groups will be allocated on a fully randomised basis. A randomization schedule will be generated by the dedicated trials pharmacy representative who has signed/dated the staff delegation log and is not otherwise associated with this study. Patients will be randomised in a 1:1 treatment allocation ratio to either AZD4017 or placebo. The randomization schedule will be stored in a password protected file accessible only to the dedicated trials pharmacy (the CI and Scientific Lead will be blinded to the randomization process) until all samples have been collected.

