### 13.4. Planned analyses

#### 13.4.1. Primary endpoint analysis

Skin 11 $\beta$ -HSD1 activity will be summarized descriptively in each treatment group at each time-point; the primary analysis will be on an intention-to-treat basis, will all patients included, as randomised. This will be supplemented by a per-protocol analysis that includes patients whose compliance with protocol is deemed satisfactory. Unadjusted and adjusted summaries (adjusted for gender, age and baseline HbA1c) for absolute values and changes from baseline will be presented; between-group differences in absolute values and changes from baseline will be presented together with 90% confidence intervals – deemed acceptable for pilot studies [65]. Adjusted summaries will be obtained via a linear regression model which mirrors analysis of covariance. Where necessary, transformations to a normal distribution will be performed. Preliminary proof-of-concept will be considered to have been achieved if adjusted mean 11 $\beta$ -HSD1 activity in skin at 28 days is lower in the active treatment arm compared to the placebo arm. Estimated sample sizes for future trials will be produced based on the pooled standard deviations from both treatment arms for the following outcomes: 11 $\beta$ -HSD1 activity in skin (at baseline and 28 days), sudomotor function, skin hydration, epidermal barrier function (at baseline and 35 days), integrity (at baseline and 28 days) and recovery (at baseline and 28 days – 3 hour, 2 day and 7 day), skin thickness (at baseline and 35 days) and wound healing (at baseline and 28 days – 2 day and 7 day). Sample sizes for a range of plausible and clinically-meaningful between-group differences will be presented, assuming analysis of covariance controlling for baseline values would be used. Correlation (Pearson's *r*) between baseline and follow-up values will be estimated in the combined treatment groups to aid in the sample size estimates. If the

correlation between the measurements at the two time-points is  $\rho$ , ANCOVA comparing groups of  $(1-\rho^2)n$  subjects has the same power as a t-test comparing groups of  $n$  subjects.

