### **13.9. Determination of sample size and randomization method**

Sample size is small as this is a preliminary pilot study and the first use in this patient group. Published rules of thumb for pilot studies recommend a sample size of 12 participants per arm completing the protocol [66]. To ensure this minimum number complete the protocol we will randomise 15 per arm to allow for 20% drop-out.

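### Sample sizes for the next trial treat the pilot's SD and correlation as known: where the pilot shows little effect, nominal 80% or 90% power would average about 75% or 85%

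*Protocol*

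**What the plan says.** Section 13.4.1 of the protocol sets the method for sizing later trials. It starts from the pilot's variability: "Estimated sample sizes for future trials will be produced based on the pooled standard deviations from both treatment arms". The list that follows covers skin 11β-HSD1 activity and the skin-function outcomes. The next step is: "Sample sizes for a range of plausible and clinically-meaningful between-group differences will be presented, assuming analysis of covariance controlling for baseline values would be used". Pearson's r "between baseline and follow-up values will be estimated in the combined treatment groups to aid in the sample size estimates". The closing sentence converts a t-test size to an ANCOVA size: ANCOVA with groups of (1−ρ²)n "subjects has the same power as a t-test comparing groups of" n.

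The between-group difference is the only quantity given a range. The SD and r get no confidence limit, range or inflation, although the same section attaches 90% confidence intervals to the between-group differences.

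Sizing the next trial is a declared use of the pilot. Section 5.3 (Safety) says: "Data collected will be used to inform powering and feasibility of a future confirmatory trial". Sections 1.3 and 9.2.4 say much the same. On the pilot's own size, section 13.9 says "Published rules of thumb for pilot studies recommend a sample size of 12 participants per arm completing the protocol" and "we will randomise 15 per arm to allow for 20% drop-out".

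**The concern.** The (1−ρ²) relation is a sound approximation for the true SD and the true correlation. Here both come from about 24 patients. Power is a concave function of the variance estimate over the range that matters: a size that is too small loses more power than an equally oversized one gains. Average delivered power therefore falls below the label even when the variance estimate is unbiased.

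The rule adds a second, avoidable error. A pooled SD on n−2 degrees of freedom multiplied by (1−r²) ignores the degree of freedom spent on the baseline slope, so the residual variance comes out too low.

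Taking r across arms brings in a third influence. A treatment effect in the pilot adds between-arm spread at follow-up that baseline cannot explain. This pulls r towards zero and pushes the size up.

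At stake is one of the pilot's main products: a table whose power labels do not match what the sizes deliver.

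**Working it through.** **The plan's own figure.** 12 completers per arm with 20% drop-out gives 12/0.80 = 15 per arm, 30 in total, as section 13.9 states. The protocol gives no size, alpha or power for the future trial, so there is no further figure to reproduce.

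**Inputs.** From the protocol: 12 completers per arm (15 if nobody drops out), 1:1 allocation, pooled SD s, Pearson r, and ANCOVA on baseline. Assumed here: two-sided 5% test, nominal power 80% or 90%, bivariate normal data, equal SDs in the two arms unless stated.

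**Formulas.** Size per arm: n = 2s²(1−r²)(z₀.₉₇₅ + z_power)²/δ². Delivered power: Φ{(z₀.₉₇₅ + z_power)·√[s²(1−r²)/(σ²(1−ρ²))] − 1.960}. The sum z₀.₉₇₅ + z_power is 2.802 for 80% and 3.242 for 90%. The difference δ cancels.

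**No effect in the pilot, r within arms.** With 24 completers, s²(1−r²) equals RSS/22, where RSS is the residual sum of squares from the model with arm and baseline, and RSS/[σ²(1−ρ²)] follows χ² on 21 df. Hence:
- The mean ratio to the true residual variance is 21/22 = 0.955, about 4.5% too low.
- The tabulated size runs from 0.60 to 1.35 times the correct one (10th to 90th percentile), median 0.92.
- The chance of falling below nominal is P(χ²₂₁ < 22) = 0.60.
- At the 10th percentile, 2.802 × √0.602 − 1.960 = 0.214, which is 58% power. The same step for nominal 90% gives 71%.

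Mean delivered power over this distribution:

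| Variance used | Nominal 80% | Nominal 90% |
|---|---|---|
| s²(1−r²), 12 per arm | 75.4% | 85.4% |
| s²(1−r²), 15 per arm | 76.3% | 86.4% |
| SD estimated, ρ known, 12 per arm | 77.2% | 86.9% |
| Residual variance on 21 df | 77.1% | 86.7% |
| One-sided 80% upper limit of residual variance, 21 df | 87.2% | 93.8% |

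Uncertainty in the SD alone costs 2 to 3 points. The rest comes from estimating r and not counting the degree of freedom used by the slope.

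**The protocol's r across arms, by simulation, 12 per arm.**

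| Pilot effect (SD) | ρ | Nominal 80% | Nominal 90% |
|---|---|---|---|
| 0 | 0.3 to 0.7 | 75% | 85% |
| 0.5 | 0.3 to 0.7 | 76 to 78% | 86 to 87% |
| 1 | 0.5 | 78% | 88% |
| 1 | 0.7 | 82% | 91% |
| 2 | 0.5 | 81% | 90% |
| 2 | 0.7 | 89% | 95% |

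With no effect, about 60% of trials again fall below nominal. With a 2 SD effect and ρ = 0.7, the mean r drops to 0.48 and the variance entered averages 1.43 times the true one.

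**Upper limit.** χ² on 21 df at 0.20 is 15.44. The size at the one-sided 80% limit is 21/15.44 = 1.36 times the residual-variance size and 22/15.44 = 1.42 times the within-arm s²(1−r²) size. By construction, 20% of trials are then underpowered.

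**The case against.** Four things can be said for the plan.

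- **The shortfall is not general.** A reader might infer that every size in the future table is too small and that 75% or 85% is what the rule delivers for all outcomes. The documents do not support that, because r is taken across arms. For skin 11β-HSD1 activity a large effect is what the design hopes for: section 5.3 (Dose) cites about 90% inhibition of the enzyme. Suppose activity in the active arm falls by 50 to 90% with its SD shrinking in proportion, the baseline mean is 2 to 3 SDs and ρ is 0.3 to 0.7 (all assumptions). Mean power at nominal 80% is then about 75 to 86%. This objection stands and limits the point. It is not a defence of the rule, since the offset depends on the size of the pilot effect and cannot be counted on for the skin-function outcomes.
- **No alpha or power is stated.** This is true. The figures illustrate conventional choices.
- **The analysis plan could add a range for the SD or r.** It could, and nothing in section 13.4.1 forbids it. The section nevertheless states the method itself and varies only the difference, and the uncounted degree of freedom is part of that method.
- **An 80% upper limit is only one convention.** This also stands. With r across arms and no pilot effect, multiplying the size by about 1.13 (80%) or 1.18 (90%) would restore average power, so the 80% limit goes further than that requires.

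The published rule of 12 per arm supports the size of the pilot. It does not support treating the pilot's estimates as exact.

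**Conclusion.** The point holds in a conditional form. Assuming a two-sided 5% test and 12 completers per arm, for outcomes with little or no between-arm effect in the pilot, the stated rule gives trials that average about 5 points less power than their label, and about 60% of them fall short. Where the pilot effect is large and ρ is about 0.5 or more, the loss shrinks or turns into oversizing. The tabulated sizes can thus err in either direction, and the reader of the table could not tell which.

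Nor do the documents support the inference that the pilot is too small or its own results unsound. Section 13.2 makes the analysis descriptive, and its estimates and intervals do not use this calculation. The consequence lies wholly in the planning of a later trial, so this is worth correcting before the sizes are produced but is no obstacle to the present study.

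**What to change.** In section 13.4.1, replace the pooled SD combined with (1−r²) by the residual variance from a model with arm and the outcome's own baseline value, on its own residual degrees of freedom (21 with 24 completers). This removes the low bias and, for a constant shift between arms, the dependence on the pilot effect. Mean power becomes about 77% and 87%.

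Beside each point-estimate size, tabulate the size at an upper confidence limit of that residual variance and name the level. A one-sided 80% limit, for example, gives about 87% and 94% mean power. State the alpha and power behind the table. Leave the choice of planning column to the designers of the next trial, because it trades patients against assurance.

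The cost is a sentence or two and one table column. At 12 per arm, a designer who picks the 80% limit plans for 1.36 times the residual-variance size, or 1.42 times the within-arm version of the present rule. Nothing in the pilot's conduct or analysis changes.

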### 8.2. Frequency and duration of the trial drugs

Participants will be randomised to receive either AZD4017 400mg twice daily (as close to 12 hours apart as possible) or placebo. AZD4017 or placebo will be dosed as 2 tablets orally twice daily for 35 days starting at the baseline visit (Visit 1).

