#### 9.2.3.4. Epidermal barrier recovery

In addition to resting TEWL, epidermal function can be assessed by measuring TEWL recovery over time following barrier disruption by repeated tape stripping.

Following the initial TEWL measurement, adhesive patches (D-Squame tapes) will be used to gently remove the *stratum corneum* layers to a pre-specified TEWL rate from the lower inner forearm at Visits 1 and 4. Recovery of TEWL at this location will be evaluated by repeated TEWL readings at 3 hour, 48 hour and 7 days post-disruption at Visits 1, 2, 3, 4, 5 and 6.

This procedure will be conducted by the Scientific Lead and may cause a temporary mild discomfort or transient irritation which should subside within a few hours. The results will be recorded in the CRF and stored as image files in a temporary folder (including enrolment number, visit number and date) on the secure (encrypted) laptop used for the measurements before transfer to a secure server.

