#### **9.2.3.7. Wound healing**

Both biopsies from visit 1 and two biopsies from visit 3 will be imaged by OCT at Visits 2, 3, 5 and 6. Recent studies suggest OCT may be a useful tool to evaluate wound re-epithelialization [63]. This imaging modality is already being utilised by our department [64]. OCT uses light to capture sub-micrometer resolution, three-dimensional images from within biological tissue (e.g. skin). The method is based on low-coherence interferometry, typically employing near-infrared light. The use of relatively long wavelength light allows it to penetrate 1-2mm into the tissue. In addition to wound diameter, collected images capture information on vascularization which may be used for future studies.

The procedure takes approximately 2min using a small probe applied to the skin, is non-invasive, pain-free and will be conducted by the Scientific Lead or delegated authorised personnel. Image files (including enrolment number, visit number and date) will be stored on the OCT machine until the end of the trial. They will then be transferred to a secure server, compiled, analysed and values for wound diameter entered into the CRF.

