### 13.3. General statistical considerations

Unless otherwise specified, the last valid measurement before study medication administration will be utilized as the baseline value. In general, summary statistics [n (number of available measurements), arithmetic mean, standard deviation, median, minimum, and maximum] for quantitative variables and absolute and relative frequency tables for qualitative data will be presented.

Wherever possible the trial will be reported in accordance with the recommendations of the Consolidated Standards of Reporting Trials statement.

An initial blind review of the data will be completed prior to locking the database to identify patients to be excluded from per-protocol analysis.

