#### **13.4.2. Secondary endpoint analyses**

##### **13.4.2.1. Efficacy**

Systemic 11 $\beta$ -HSD1 activity and skin function analyses will be conducted as for the primary endpoint (above). The strength of association between skin AZD4017 at day 28 concentration and plasma AZD4017 at day 35 in the active treatment arm will be assessed using Pearson's product moment correlation coefficient; for severely skewed variables for which a suitable transformation cannot be found, Spearman rank correlation will be used. For all correlation analyses, absolute correlation coefficients with a value of  $r(ho) \geq 0.3$  will be considered preliminary evidence of substantive association.

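### For wound healing and for 48-hour and 7-day barrier recovery, the readings called baseline are taken on days 2 and 7 of treatment, so change from baseline removes any early drug effect and the planned ANCOVA discount lacks a pre-treatment covariate

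*Protocol*

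**What the plan says.** Section 8.2 has study drug "dosed as 2 tablets orally twice daily for 35 days starting at the baseline visit (Visit 1"), which is day 0. Section 13.3 states the general rule that, unless otherwise specified, "the last valid measurement before study medication administration will be utilized as the baseline value".

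Section 13.4.1 asks for between-group differences in absolute values and in changes from baseline, with 90% confidence intervals. Its adjusted summaries use gender, age and baseline HbA1c. Section 13.4.2.1 extends this: "skin function analyses will be conducted as for the primary endpoint (above").

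Section 13.4.1 also lists the outcomes for which future sample sizes will be produced. They include "recovery (at baseline and 28 days – 3 hour, 2 day and 7 day") and "wound healing (at baseline and 28 days – 2 day and 7 day"). Those sample sizes assume ANCOVA controlling for baseline. They use a baseline-to-follow-up correlation estimated in both arms combined and the factor (1 − ρ²).

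On timing, section 9.2.3.4 says: "Recovery of TEWL at this location will be evaluated by repeated TEWL readings at 3 hour, 48 hour and 7 days post-disruption", with tape stripping at Visits 1 and 4. Section 9.2.3.7 says: "Both biopsies from visit 1 and two biopsies from visit 3 will be imaged by OCT at Visits 2, 3, 5 and 6". Table 1 shows wound imaging at Visits 2, 3, 5 and 6 only.

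**The concern.** A change from baseline measures a drug effect only if the baseline was taken before the drug could act. Here the first wound and the first tape-strip site recover while the patient is already taking study drug. The first-cycle readings at 48 hours and 7 days are post-randomisation outcomes under another name, and subtracting them from the second-cycle readings subtracts whatever effect AZD4017 has already had.

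Section 1.3 says the pilot is meant to inform power calculations for a future trial of foot ulcer healing, and wound healing is in the trial's title. A between-arm change score near zero could then reflect either an inactive drug or an effect of equal size in both cycles, and nothing in section 13.4 would warn the reader. The sample sizes carried forward would also rest on a correlation between two on-treatment readings, presented as a correlation with baseline.

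**Working it through.** **Plan's own figure.** Section 13.9 wants 12 completers per arm with 20% drop-out: 12 / (1 − 0.20) = 15 per arm, as stated. This is correct and does not bear on the point; 12 per arm is used in the simulation below.

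**Step 1: study day of each reading** (sections 8.2, 9.2.3.4, 9.2.3.7, 10.3 to 10.8 and Table 1; first dose on day 0)

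| Outcome | First cycle, called baseline | Second cycle |
|---|---|---|
| Wound healing, 2 day | day 2 | day 30 |
| Wound healing, 7 day | day 7 | day 35 |
| Barrier recovery, 3 hour | day 0 | day 28 |
| Barrier recovery, 48 hour | day 2 | day 30 |
| Barrier recovery, 7 day | day 7 | day 35 |

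Both wound readings and two of the three recovery readings called baseline fall after dosing has begun. The 3-hour reading is on day 0. Section 10.3 lists tablet collection (item 7) before that reading (item 10) but does not fix the time of the first dose, so its status is open.

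**Step 2: what each contrast estimates.** Let D be the true between-arm effect in the second cycle, f the share of D already present in the first cycle, and ρ the within-arm correlation between cycles, with equal SDs. Neither f nor ρ is in the protocol; f from 0 to 1 and ρ of 0.3, 0.5 and 0.7 are assumptions.

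- Absolute difference, second cycle: D
- Difference in change from baseline: D − fD = (1 − f)D
- ANCOVA on the first-cycle value: D − ρfD = (1 − ρf)D

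Share of D kept:

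| f | Absolute | Change | ANCOVA, ρ = 0.3 | ANCOVA, ρ = 0.5 | ANCOVA, ρ = 0.7 |
|---|---|---|---|---|---|
| 0 | 1.00 | 1.00 | 1.000 | 1.000 | 1.000 |
| 0.25 | 1.00 | 0.75 | 0.925 | 0.875 | 0.825 |
| 0.5 | 1.00 | 0.50 | 0.850 | 0.750 | 0.650 |
| 0.75 | 1.00 | 0.25 | 0.775 | 0.625 | 0.475 |
| 1 | 1.00 | 0.00 | 0.700 | 0.500 | 0.300 |

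Simulation with 12 per arm, D = 1 SD, ρ = 0.5 and 20,000 runs agrees. For absolute, change and ANCOVA in turn it gave 1.00, 1.00 and 1.00 at f = 0; 1.00, 0.50 and 0.75 at f = 0.5; and 1.00, 0.00 and 0.51 at f = 1.

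The change column applies to an analysis planned in this trial. The ANCOVA columns apply only to the future trials that section 13.4.1 sizes.

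**Step 3: the correlation carried forward.** With arms combined and v = D²/4 = 0.25 for D = 1 SD, the correlation is (ρ + fv) / √[(1 + f²v)(1 + v)]. For a within-arm ρ of 0.50 this gives 0.447, 0.542 and 0.600 at f = 0, 0.5 and 1. The factor (1 − ρ²) becomes 0.80, 0.71 and 0.64, against 1 − 0.50² = 0.75. So at f = 0.5 the sample size is about 6% too small (0.706 / 0.75 = 0.94), and at f = 1 about 15% too small (0.64 / 0.75 = 0.85). The departure at f = 0 comes from combining the arms, not from this point.

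**Step 4: if the next trial repeats the design.** Suppose it takes its covariate on treatment, is sized on the full D, and applies the discount. ANCOVA then targets (1 − ρf)D, so it would need 1 / (1 − ρf)² times the patients. At f = 0.5 that is 1 / 0.75² = 1.8 times for ρ = 0.5, and 1 / 0.65² = 2.4 times for ρ = 0.7.

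**The case against.** The case against is substantial, and most of it stands as a limit on the point.

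- **The valid contrast is already planned.** Section 13.4.1 requires absolute between-group differences as well as changes, and section 13.4.2.1 carries both to skin function. This stands: the fault lies in a companion summary shown beside a sound one. A reader might infer that the trial would make an active drug look inert. That would need f close to 1 and a reader who ignored the absolute differences.
- **The in-trial adjusted models are not shown to adjust for the first cycle.** Their listed covariates are gender, age and baseline HbA1c. It is tempting to say that the adjusted results also lose part of the effect, but the protocol does not support that. ANCOVA on the outcome's own baseline appears only in future sample sizing.
- **Section 13.3 allows exceptions, and the label may be shorthand.** Section 3.2 lists baseline separately from days 2 and 7, so baseline in section 13.4.1 may mean the Visit 1 wound and tape-strip cycle. This softens the charge of contradiction. It does not remove the problem, because no wording turns a reading after randomisation and dosing into a valid baseline, and section 13.4.1 does not say these readings are on treatment.
- **The size is assumed.** The early inhibition data in sections 5.3 and 8.6 concern liver and urinary markers, and sections 1.1 and 5.3 say the effect in peripheral tissue in man is unknown. This stands: f above zero is plausible but not established.
- **Future sizing does not use the observed change.** It uses pooled SDs and a range of plausible differences. A reader might apply 1 / (1 − f)², a fourfold inflation at f = 0.5, but that describes a method the protocol does not use.

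**Conclusion.** The point holds in limited form. For wound healing and for 48-hour and 7-day barrier recovery there is no pre-treatment value, and the first-cycle readings that section 13.4.1 calls baseline are on-treatment outcomes, in conflict with the rule in section 13.3. The between-arm change from baseline keeps (1 − f) of the later effect. That is anything from all of it to none, depending on an f the protocol does not give. It is unbiased only if the drug has no effect on these outcomes by days 2 and 7.

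The future sample sizes for these outcomes are also affected, because a (1 − ρ²) discount is planned without a pre-treatment covariate to support it. The error in the discount itself is modest under the assumptions in step 3. It is larger only if the next trial copies the on-treatment baseline.

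The absolute between-arm differences, the primary endpoint, the proof-of-concept rule, resting barrier function, integrity, hydration, sudomotor function and skin thickness are not affected. Section 4.2 classes wound healing and barrier recovery as exploratory, and section 13.2 makes the whole analysis descriptive. Severity is therefore moderate.

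**What to change.** In sections 13.4.1 and 13.4.2.1, for wound healing and for 48-hour and 7-day barrier recovery:

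- Relabel the two cycles as early on-treatment (days 0 to 7) and late on-treatment (days 28 to 35).
- Report between-arm differences in absolute values, with their 90% intervals, for each cycle, and omit change from baseline.
- Quote future sample sizes for these outcomes without the (1 − ρ²) discount.
- Use the Visit 1 3-hour recovery reading as a baseline only where it is recorded as preceding the first dose.

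Separately, and as a clerical matter, reconcile the Visit 3 biopsies mentioned in section 9.2.3.7 with the schedule, which takes biopsies at Visits 1 and 4.

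The cost is wording only; no visit, procedure or measurement changes. The change score for these outcomes is lost, but it was never a change from a pre-treatment value. Future sample sizes quoted for them will be larger by the factor 1 / (1 − ρ²), for example 1 / 0.75 = 1.33 at ρ = 0.5.

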### **Dose**

AZD4017 is a novel orally bioavailable small molecule inhibitor of 11 $\beta$ -HSD1 enzyme activity. It is potent and highly selective *in vitro* and *in vivo*. The half maximal inhibitory concentration (IC50) for inhibition of 11 $\beta$ -HSD1 activity (cortisone to cortisol conversion) is 2nM. AZD4017 is selective (> 2000x) for 11 $\beta$ -HSD1 over human recombinant 11 $\beta$ -HSD2 and the closely-homologous enzymes 17 $\beta$ -hydroxysteroid dehydrogenase 1 (17 $\beta$ -HSD1) and 17 $\beta$ -hydroxysteroid dehydrogenase 3 (17 $\beta$ -HSD3) *in vitro*.

The dose to be used in this study is 400mg twice daily. This dose results in a decrease in the urinary ratio of tetrahydrocortisol to tetrahydrocortisone metabolites ([THF+alloTHF]/THE) from 0.99+0.27 to 0.11+0.06 and decreases the generation of plasma prednisolone following oral prednisone by 80%. Pharmacokinetic and pharmacodynamic data from single and multiple ascending dose studies in healthy volunteers suggest that a dose of 400mg twice daily may achieve approximately 90% inhibition of 11 $\beta$ -HSD1 over 24 hours. The safety and tolerability profile of AZD4017 has been studied in animals and in single and multiple ascending dose studies in human volunteers and supports the use of AZD4017 twice daily to 900 mg/day. The 35-day treatment period is considered sufficient to see sustained inhibition of 11 $\beta$ -HSD1 by AZD4017, and therefore this dose and duration is appropriate. Please refer to IB for more information.

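### The baseline-to-follow-up correlation for future sample sizes is taken across both arms together, but the ANCOVA rule needs the within-arm correlation; in expectation the future n comes out too large wherever the drug has an effect

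*Protocol*

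**What the plan says.** Protocol section 13.4.1 sets out how the pilot's data will be turned into sample sizes for later trials.

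- **SD:** "Estimated sample sizes for future trials will be produced based on the pooled standard deviations from both treatment arms". The outcomes listed are skin 11β-HSD1 activity (named first), sudomotor function, skin hydration, the barrier measures, skin thickness and wound healing.
- **Effect sizes:** "Sample sizes for a range of plausible and clinically-meaningful between-group differences will be presented", with no figures given.
- **Future analysis:** "assuming analysis of covariance controlling for baseline values would be used".
- **Source of r:** a Pearson coefficient is to be used; the association "between baseline and follow-up values will be estimated in the combined treatment groups to aid in the sample size estimates".
- **Rule:** with correlation rho between the two time-points, ANCOVA on groups of (1-rho^2)n "has the same power as a t-test comparing groups of" n.

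Nothing in the section says that r is computed within arms, averaged over arms or adjusted for treatment. Section 13.4.3 does plan partial correlation where a third variable has to be allowed for, but for a different purpose.

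**The concern.** ANCOVA has a treatment term, so its residual variance is the within-arm follow-up variance multiplied by (1-rho^2), where rho is the within-arm correlation. When both arms are put into one Pearson correlation, the drug-placebo gap at follow-up inflates the follow-up variance. Under randomisation it adds nothing, in expectation, to the covariance with baseline. The estimate of r is therefore diluted, and more so the larger the treatment effect.

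Informing the size of a later trial is a stated purpose of this pilot (sections 1.3, 5.3 under Safety, and 9.2.4). A diluted r asks the next trial for more patients than it needs, and most of all for the outcomes that respond best to the drug.

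**Working it through.** **Inputs from the protocol.** Allocation is 1:1: "Patients will be randomised in a 1:1 treatment allocation ratio to either AZD4017 or placebo" (section 6.4.3). Section 13.9 cites rules of thumb that "recommend a sample size of 12 participants per arm completing the protocol"; 12/(1-0.20) = 15 randomised per arm, which reproduces the pilot's size. No r, SD, alpha, power or future n is given. Within-arm rho and the effect d (in within-arm SDs at follow-up) are therefore assumptions, shown over a range.

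**Step 1: the rule itself.** Assume a future difference of 0.5 SD, two-sided 5% and 80% power. The t-test needs 63 per arm (power 0.801). With within-arm rho = 0.7, ANCOVA on 63 × (1-0.49) = 32.13 per arm with residual SD √0.51 also has power 0.801. The rule is right when rho is the within-arm correlation.

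**Step 2: what the combined correlation estimates.** At 1:1 with equal SDs and no baseline imbalance, the combined follow-up variance is the within-arm variance times (1 + d²/4), and the covariance is unchanged. Hence

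r_combined = rho / √(1 + d²/4), and excess = (1 - r_combined²)/(1 - rho²) - 1.

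| d | rho 0.6: r | 1-r² (correct 0.64) | excess | rho 0.7: r | 1-r² (correct 0.51) | excess |
|---|---|---|---|---|---|---|
| 0 | 0.600 | 0.640 | 0% | 0.700 | 0.510 | 0% |
| 0.5 | 0.582 | 0.661 | 3% | 0.679 | 0.539 | 6% |
| 1 | 0.537 | 0.712 | 11% | 0.626 | 0.608 | 19% |
| 2 | 0.424 | 0.820 | 28% | 0.495 | 0.755 | 48% |

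At d = 0.5, 1 and 2 the excess is 2%, 7% and 17% with rho = 0.5, and 10%, 36% and 89% with rho = 0.8.

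In the step 1 example with rho = 0.7, the correct 33 per arm becomes 34, 39 or 48 at pilot effects of d = 0.5, 1 or 2.

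**Step 3: behaviour at the pilot's size.** In 20,000 simulated pilots with 12 per arm and rho = 0.7, mean combined r was 0.670, 0.615 and 0.475 at d = 0.5, 1 and 2, against about 0.69 pooled within arms. The dilution is an expectation: combined r² exceeded within-arm r² in about 30%, 13% and 4% of those pilots, because chance baseline imbalance can add covariance.

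**Step 4: a rough proxy for a large effect.** The only mean-and-SD pair in the protocol is the urinary metabolite ratio on the trial dose, "from 0.99+0.27 to 0.11+0.06" (section 5.3, Dose), read here as mean and SD. Take baseline SD 0.27 in both arms, follow-up SDs 0.27 (placebo) and 0.06 (active), a gap of 0.88 and the same rho in each arm.

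- Mean of the follow-up SDs: (0.27 + 0.06)/2 = 0.165.
- Pooled within-arm follow-up SD: √((0.27² + 0.06²)/2) = 0.196.
- Combined follow-up SD: √(0.03825 + 0.88²/4) = 0.4815.
- Pooled within-arm r = rho × 0.165/0.1956 = 0.844 rho.
- Combined r = rho × 0.165/0.4815 = 0.343 rho.
- rho = 0.6: (1 - 0.206²)/(1 - 0.506²) = 0.958/0.744, an excess of 29%.
- rho = 0.7: (1 - 0.240²)/(1 - 0.591²) = 0.942/0.651, an excess of 45%. Simulation at 12 per arm gave 0.91/0.64, about 42%.

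**The case against.** **Direction.** The expected error oversizes a later trial and does not underpower it. This stands. A reader might infer from the chance-imbalance cases that future trials will be undersized. The plan gives no basis for that: such cases are sampling variation around an estimate that is biased the safe way.

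**Imprecision.** With 24 completers, an observed r of 0.6 has a 95% interval of about 0.26 to 0.81, so 1-r² could lie anywhere from 0.93 to 0.35. Against that, an excess of 6% is minor, and the protocol presents a range of sizes, not one n. This also stands, but wide sampling error is no reason to keep a systematic bias that costs nothing to remove.

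**Relevance.** Section 1.3 aims the next trial at foot ulcer healing, so skin enzyme activity may not drive its size. For skin-function outcomes the protocol gives no effect size, and with modest effects the error is small. This limits the point without removing it, since enzyme activity is on the list for which sample sizes will be produced.

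**A tempting larger figure.** A reader might put the urinary figures into the equal-SD formula (0.88/0.196 = 4.5 SDs) and obtain an excess of 47% at rho 0.6 or 80% at rho 0.7. The documents do not support this. The two SDs are far from equal, the contrast is before versus after dosing, the urinary ratio is not on the outcome list for future sample sizes, and sections 1.1 and 5.3 say that the effect in peripheral tissue such as skin is not known.

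**Wording.** The sponsor may have meant a within-arm correlation pooled over arms. The text does not say so. Equally, it does not define the pooled SD as within-arm, so a mismatch between SD and r is likely but not stated. If both ignored treatment arm, the error would grow: the residual variance would be proportional to 1 + d²/4 - rho², which at d = 1 and rho = 0.7 is 0.76 against 0.51, an excess of 49%.

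**Conclusion.** The point holds. As written, section 13.4.1 feeds a combined-arm correlation into a rule that needs the within-arm one. In expectation the future n is too large by about 6% or less at d = 0.5, 11 to 19% at d = 1 and 28 to 48% at d = 2, for rho between 0.6 and 0.7; at d = 0 the two approaches agree. These figures assume 1:1 allocation, equal SDs and the stated values of rho and d, none of which except the allocation is in the protocol. The urinary proxy of 29 to 45% shows only the order of magnitude a large biochemical effect could produce.

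The error is conservative and confined to planning later trials. It does not touch this pilot's 15 per arm, its treatment comparison, its 90% confidence intervals or its proof-of-concept criterion. It should be corrected because future sample sizes are a declared output of the pilot.

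**What to change.** In section 13.4.1, say that r will be estimated as the pooled within-arm correlation (partial correlation given treatment arm) and reported with its confidence interval, in place of the combined-group estimate. Alternatively, take the residual SD directly from an ANCOVA with treatment and baseline, which needs no separate r. In the same sentence, state that the pooled SD is the within-arm pooled SD.

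The cost is one phrase. It needs the same data and software, changes nothing for participants, and can be settled before the database is unblinded.
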